### Statistical analysis

Baseline descriptive data will be presented as mean ± standard deviations (SD). Differences in clinical and echocardiographic variables will be assessed by unpaired Student's *t *test. Differences between proportions will be assessed by chi-square analysis; a Fisher's exact test will be used when appropriate. Event-free survival curves are computed with the Kaplan-Meier method, and the differences between these curves are tested with a Mantel-Cox log-rank test. A primary endpoint analysis is planned at 30 days, 6 months, and 1 year of follow-up. Subgroup analyses are planned to determine whether the treatment effect is more or less pronounced in certain subgroups. The data will be subgrouped by sex, age, diabetes, anterior infarction, time from onset of symptoms to treatment, and the use of thrombolytics. All analyses will be performed on an intention-to-treat basis. Also, the outcome per-protocol will be evaluated. Such an analysis seems worthwhile, as it will reflect the true influence of PCI on post-thrombolytic ischemic events.

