## Methods

### Patient Selection

Patients admitted to any of the participating centers with an acute or recent myocardial infarction, who are not treated by direct or rescue angioplasty, and who are stable during the first 48 hours after the acute event, are screened for the study. Patients < 80 years of age are considered suitable for the study when they have definite myocardial infarction, as demonstrated by an significant rise in creatine kinase-MB levels (twice the upper limit of normal: ULN), 1 mm ST segment elevation in two or more standard leads or 2 mm ST segment elevation in two contiguous chest leads, and/or the development of Q waves.

The criteria for exclusion are: viability testing technically not possible (poor echo-window), contraindications for dobutamine echocardiography (arrhythmia), and coronary angiography (severe diabetic nephropathy or known contrast-allergy), serious life-threatening non-cardiac illness, ECG abnormalities making the evaluation of the ST segment impossible (left bundle branch block, pacemaker), and an unreliable follow-up.

The study complies with the Declaration of Helsinki and all ethics committees of the participating centers have approved the protocol. All eligible patients provide written informed consent.

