### Study design

The study is a prospective, multicenter, randomized, controlled clinical trial. In the VIAMI-trial, patients who are admitted to the hospital with an acute myocardial infarction and who did not undergo primary or rescue PCI, are evaluated by LDDE within 3 days of admission. Patients with unequivocal signs of viability in the infarct-area are randomized to an invasive or a conservative treatment strategy. In the invasive strategy patients undergo coronary angiography with the intention to perform PCI with stenting of the infarct-related coronary artery. In the conservative group an ischemia-guided approach is adopted with stress testing before discharge from the hospital. When the test is highly suggestive for ischemia, coronary angiography will be performed. If revascularization is performed, this will be scored as a secondary endpoint. Patients without viability will serve as a registry group with long-term follow-up (Fig 1). These patients are assigned to the conservative group in order to prevent physicians' bias during the trial.

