**Figure 1 F1:**
[figure not shown]
Flow chart

The primary endpoint is the composite of death from any cause, recurrent infarction, and unstable angina. The secondary endpoints are need for revascularization, the occurrence of angina pectoris (CCS classification), and the incidence of heart failure (NYHA classification). Left ventricular function is also evaluated as determined by echocardiography at 3 months, 6 months, and 1 year follow-up.

A reinfarction is diagnosed if there is an increase in the total creatine kinase and MB isoenzyme activity (2 times ULN) and either a history of ischemic chest discomfort, or electrocardiographic changes indicative for transmural ischemia or necrosis.

For the diagnosis of unstable angina, the patient must be hospitalized with ischemic chest pain or discomfort occurring at rest or with minimal exertion. In addition, the need for intravenous medical intervention and/or objective evidence of myocardial ischemia is required. For extensive description of the end points definitions, see Table I.

**Table I T1:** Primary end point definitions

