### Low-dose dobutamine echocardiography

If the inclusion criteria are met and none of the criteria for exclusion, viability testing by LDDE is performed within 3 days of admission.

Preferably, beta-blockers are withdrawn 24 hours before the test [23,27,30,31]. Discontinuation of beta-blockers seems to to enhance LDDE accuracy [45,46]. Before the administration of dobutamine, a baseline echocardiogram is obtained according to the guidelines of the American Society of Echocardiography [47]. Five standard views are obtained: the parasternal long-axis and short-axis view and the apical two, three- and four-chamber view. A 16-segment model is used in which the apex is divided in 4 segments. Segmental wall motion and thickening is scored according to a 4-point scale: 1 = normal, 2 = hypokinetic, 3 = akinetic, and 4 = dyskinetic. Left ventricular volumes and ejection fraction are measured by use of the modified Simpson's rule algorithm from orthogonal apical long-axis projections as recommended by the American Society of Echocardiography.

Dobutamine is administrated intravenously at doses of 5, 10, and 15 μg/kg/min, for 5 minutes at each dose. When a 10% increase in heart rate is not achieved with 15 μg/kg/min, a 5-minute infusion with 20 μg/kg/min can be used as the final stage of the procedure.

Viability is defined as the improvement of wall motion abnormalities in two or more segments of the infarct zone. Changes from hypokinesia to normokinesia and from dyskinesia or akinesia to hypo- or normokinesia are considered an improvement in wall motion abnormality. Dyskinesia changing to akinesia is not considered as an improvement. Patients are continuously monitored by a 12 lead ECG and blood pressure is recorded at the end of each stage. All views are recorded at rest and during dobutamine on VHS videotape. All videotapes are sent to the core-lab (VU University medical center) and will be analyzed by 2 experienced observers. A third observer is used in case of disagreement to reach consensus.

For subsequent off-line analysis, the echocardiographic images will be digitized from VHS videotape and transferred to a working station (Enconcert^® ^by Philips). The images will be displayed side-by-side in a quadscreen format to facilitate the comparison of images.

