### Follow-up

Patients will be followed for a period of three years. Follow-up data will be obtained of all patients during visits at the outpatient clinic in the first year, and by telephone interview in the second and third year of follow-up. Left ventricular function (volumes and ejection fraction) is determined by echocardiography at 3 months, 6 months, and 1 year of follow-up.

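### The only test named for echocardiographic variables, an unpaired t test, makes no use of the pre-randomization left ventricular volumes and ejection fraction; if used at follow-up it is valid but less precise than the data allow (minor).

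*Protocol article*

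**What the plan says.** All references are to the protocol article.

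- **Test.** Statistical analysis: "Differences in clinical and echocardiographic variables will be assessed by unpaired" Student's t test. The preceding sentence reads "Baseline descriptive data will be presented as mean" with standard deviations. No other method is given for a continuous echocardiographic variable, and no covariate, change score or repeated-measures model is mentioned.
- **Baseline measurement.** Low-dose dobutamine echocardiography: "Before the administration of dobutamine, a baseline echocardiogram is obtained", and in the same description "Left ventricular volumes and ejection fraction are measured by use of the modified" Simpson's rule.
- **Timing relative to randomization.** Study design: "Patients with unequivocal signs of viability in the infarct-area are randomized to an invasive or a conservative treatment strategy". The test therefore comes before allocation. Patient Selection also excludes patients with "viability testing technically not possible (poor echo-window").
- **Follow-up measurement.** Study design, after the secondary endpoints: "Left ventricular function is also evaluated as determined by echocardiography at 3 months, 6 months, and 1 year follow-up". The Follow-up section names the variables: "Left ventricular function (volumes and ejection fraction) is determined by echocardiography at 3 months, 6 months, and 1 year of follow-up".

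**The concern.** The same quantities are measured before randomization and at three later visits, yet the one test named for them does not take the baseline value as a covariate. An early ejection fraction usually carries information about a later one in the same patient. A comparison that ignores it treats stable between-patient differences as noise.

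Two things are at stake. The confidence interval for the treatment effect on left ventricular function is wider than the collected data require. And if the arms happen to differ in baseline ejection fraction, part of that difference stays in the estimated effect.

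The outcome is secondary in rank but not incidental. The Background gives prevention of deteriorating left ventricular function as one purpose of treatment after risk assessment, and it discusses recovery of function as a way in which viability might improve survival.

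**Working it through.** **The plan's own figure.** There is none for left ventricular function. The 200 patients per group in Statistical design are derived from the clinical event rate. That number is used here only as a group size; the variance ratios do not depend on it.

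**Does each randomized patient have a baseline value?** Randomization requires viability on dobutamine echocardiography, a baseline echocardiogram precedes dobutamine, volumes and ejection fraction are measured, and patients in whom testing is technically impossible are excluded. So a pre-randomization value should exist for each randomized patient. This follows from putting the sections together; the article does not state it in one sentence.

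**Assumptions.** The correlation r is not given, so 0.3 to 0.8 is an assumed range. Also assumed: equal variance at baseline and follow-up, the same r in both arms, and complete echocardiographic follow-up at 200 per arm.

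**Variance of the treatment contrast**, with the t test on follow-up values set to 1:

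- t test on change from baseline: 2(1 − r)
- ANCOVA with baseline as covariate: 1 − r²
- change t test relative to ANCOVA: 2(1 − r)/(1 − r²) = 2/(1 + r)

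**Detectable difference** at 80% power and two-sided 0.05: (1.960 + 0.842) × √(2/200) = 0.280 SD for the t test on follow-up values. The ANCOVA figure is 0.280 × √(1 − r²), and the change figure is 0.280 × √(2(1 − r)).

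| Assumed r | ANCOVA ÷ follow-up t test | Change t test ÷ ANCOVA | Per-arm n for a follow-up t test to match ANCOVA with 200, 200/(1 − r²) | Detectable difference, ANCOVA (SD) | Detectable difference, change t test (SD) |
|---|---|---|---|---|---|
| 0.3 | 0.91 | 1.54 | 220 | 0.267 | 0.331 |
| 0.5 | 0.75 | 1.33 | 267 | 0.243 | 0.280 |
| 0.7 | 0.51 | 1.18 | 392 | 0.200 | 0.217 |
| 0.8 | 0.36 | 1.11 | 556 | 0.168 | 0.177 |

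ANCOVA is the most precise of the three in every row. Below r = 0.5 the change score does worse than ignoring the baseline: at r = 0.3 its variance is 2 × 0.7 = 1.4 times that of the follow-up t test.

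**Chance imbalance.** With 200 per arm the standard error of the baseline difference is √(2/200) = 0.10 SD. An imbalance of 1.96 standard errors is 0.196 SD. On average a fraction r of it carries into the unadjusted follow-up difference:

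- r = 0.3: 0.3 × 0.196 = 0.06 SD
- r = 0.5: 0.5 × 0.196 = 0.10 SD
- r = 0.7: 0.7 × 0.196 = 0.14 SD

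The standard error of the follow-up difference is also 0.10 SD, so these shifts are 0.6, 1.0 and 1.4 standard errors. An imbalance that large is uncommon, and a typical one does proportionately less.

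**The case against.** **The sentence may concern baseline comparisons only.** It directly follows the sentence on baseline data and pairs clinical with echocardiographic variables, as a baseline table would. On that reading the article gives no follow-up method for left ventricular function, and leaving that method to a full protocol or analysis plan would be no fault. This stands as a possible reading, and it makes the point conditional. It does not remove it: the sentence is not limited to baseline, and it is the only method stated for these variables.

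**A t test on change would use the baseline.** It would, and it fits the words equally well. Against that version the gain from ANCOVA is much smaller, a factor of 1.11 at r = 0.8, though ANCOVA remains at least as precise.

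**The correlation may be low.** Baseline is taken within 3 days of admission in patients selected for viable myocardium that may recover, so a high r cannot be presumed. At r = 0.3 the variance reduction against the follow-up t test is only 9%.

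**The t test is valid.** It is. Under randomization it is unbiased, keeps its type I error, and has a standard error that already allows for chance imbalance.

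**Stronger readings that a reader might infer.** One is that three separate unadjusted tests will be run, and that patients with a missing visit will be dropped. The article says neither: it does not state how many tests are run, whether raw or change values are compared, or how missing echocardiograms are handled. Another is that any baseline imbalance passes in full into the result; only the fraction r does.

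**Conclusion.** The point holds in a limited form. If the unpaired t test is the follow-up analysis of volumes and ejection fraction, it is valid but less efficient than the collected data permit, and it leaves part of any chance baseline imbalance in the estimate.

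The size depends on r, which the article does not give, and on the version of the t test intended. Over the assumed range 0.3 to 0.8, ANCOVA cuts the variance by 9% to 64% against a t test on follow-up values. A t test on change has 1.54 down to 1.11 times the ANCOVA variance.

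Severity is minor. Left ventricular function is mentioned after the listed secondary endpoints, no contrast on it is powered, and the primary analysis of death, reinfarction and unstable angina is unaffected. A charge of bias or of inflated type I error would not be supported.

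**What to change.** In Statistical analysis, state that follow-up left ventricular volumes and ejection fraction are compared between arms by ANCOVA with the patient's baseline echocardiographic value as covariate. A mixed model over 3, 6 and 12 months with the same covariate is an alternative. Confine the unpaired t test to description at baseline. That also settles whether the present sentence was meant for baseline or follow-up.

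If the mixed model is chosen, add a sentence on deaths. Death is a component of the primary endpoint, and echocardiographic values after death are not simply missing at random, so the model's handling of absent visits should not be taken to cover them.

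The cost is analysis wording only. The baseline and follow-up measurements are already planned, so no new data, visits or patients are needed.

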**Conclusion:**

The primary objective of the VIAMI-trial is to demonstrate that angioplasty of the infarct-related coronary artery with stenting and concomitant use of abciximab results in a clinically important risk reduction of future cardiac events in patients with viability in the infarct-area, detected early after myocardial infarction.

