### Statistical design

The VIAMI-trial is conducted to investigate the differences in clinical outcome between an invasive and a conservative strategy in patients with demonstrated viability in the infarct-area. The expected event rate in the viability positive group is estimated to be 35 percent. To demonstrate with a power of 80% (α = 0.05, two-sided) that PCI leads to a 50% reduction in event rate in the invasive group compared to the conservative group, 200 patients will be needed in each group. Therefore, we intend to randomize a total of 400 patients in this trial, with interim analysis after 200 included patients.

The formal stopping rules for the study are the following: If one of the treatment strategies appears significant superior at interim analysis (P ≤ 0.01), the study will be stopped.

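### The unadjusted log-rank or chi-square comparison of the composite endpoint is valid but forgoes some efficiency that baseline variables already collected could give

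*Protocol article*

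**What the plan says.** The Statistical analysis section compares proportions by chi-square or Fisher's exact test. For Kaplan-Meier event-free survival it states that "the differences between these curves are tested with a Mantel-Cox log-rank test". Analyses are by intention to treat, with a per-protocol evaluation added. No covariate, hazard ratio, risk difference or confidence interval is named.

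The same section plans subgroup analyses: "The data will be subgrouped by sex, age, diabetes, anterior infarction", followed by time from symptom onset to treatment and use of thrombolytics. The section on low-dose dobutamine echocardiography describes a resting echocardiogram before dobutamine is given and says "Left ventricular volumes and ejection fraction are measured by use of the modified" Simpson's rule. Under Study design, this test comes before randomization.

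The abstract's conclusion states the objective as showing that the intervention "results in a clinically important risk reduction of future cardiac events". The Current status section reports that an interim analysis of 200 patients has been done and that continuation was recommended.

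**The concern.** The trial records several plausible predictors of outcome before randomization and considers most of them worth a subgroup analysis, yet none enters the stated comparison of the composite endpoint. In a time-to-event analysis, adjustment for prognostic baseline variables usually raises power at the same type I error. It also makes the treatment estimate less dependent on how those variables happened to fall between the arms.

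A second, smaller matter is that the objective concerns the size of a reduction, while the named tests return a P value. A between-arm contrast with its interval would answer the objective directly. At stake are some power, if the true effect is smaller than planned, and a clearer reading of the result. The validity of the test is not in question.

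**Working it through.** **Inputs from the Statistical design section.**
- Event rate: "The expected event rate in the viability positive group is estimated to be 35 percent", read here as the three-year risk in the conservative arm.
- Effect: "PCI leads to a 50% reduction in event rate in the invasive group compared to the conservative group", so 35% against 17.5%.
- Error rates: "To demonstrate with a power of 80% (α = 0.05, two-sided".
- Size: "200 patients will be needed in each group".

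**Input not in the article.** The strength of the baseline predictors is assumed. It is expressed as the standard deviation (SD) of a prognostic score on the log-hazard scale and varied from 0.3 to 1.0.

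**1. The plan's own sample size.** With mean risk 0.2625, n per arm = [1.96 × √(2 × 0.2625 × 0.7375) + 0.8416 × √(0.35 × 0.65 + 0.175 × 0.825)]² / 0.175² = (1.2196 + 0.5132)² / 0.030625 = 98.05, so 99 per arm, or 110 with continuity correction. The stated 200 per group is not reproduced; 2 × 99 = 198 matches 200 only as a total. That is a separate matter. Here it means that 200 per arm leaves much spare power at the planned effect.

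**2. Unadjusted power with 200 per arm.**
- 35% against 17.5%: Φ[(0.175 − 1.96 × 0.0440) / 0.0431] = Φ(2.06) = 98.0%. For the log-rank test, the hazard ratio is ln(0.825) / ln(0.65) = 0.447 and expected events are 70 + 35 = 105. Power is Φ(√(105/4) × 0.806 − 1.96) = Φ(2.17) = 98.5%.
- One-third reduction, 35% against 23.3%: Φ[(0.1167 − 1.96 × 0.0455) / 0.0451] = Φ(0.61) = 73%.
- Power is about 80% at a 36% reduction.

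**3. Gain from adjustment.** Simulated trials with exponential event times, censoring at three years and 200 per arm:

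| Reduction | Assumed score SD | Unadjusted | Adjusted Cox | Gain (points) |
|---|---|---|---|---|
| 50% | 0.5 | 97.5% | 98.1% | 0.6 |
| 50% | 0.75 | 98.4% | 99.5% | 1.1 |
| 50% | 1.0 | 98.8% | 99.9% | 1.1 |
| 37% | 0.5 | 83.3% | 86.3% | 3.0 |
| 37% | 0.75 | 84.5% | 90.4% | 5.9 |
| 37% | 1.0 | 83.4% | 93.2% | 9.8 |
| One third | 0.5 | 73% | 76% | 3 |
| One third | 0.8 | 73% | 82% | 9 |

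Another set of runs at a one-third reduction gave gains of about 0, 6 and 10 points at SDs of 0.3, 0.5 and 0.8. The runs differ by about 3 points at SD 0.5, so the gain at that effect is best read as a range of roughly 0 to 10 points. An SD of 0.5 corresponds to a C-index of about 0.63, and 0.8 to about 0.70.

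**4. Type I error.** With no treatment effect, the log-rank test rejected in 4.5 to 5.1% of simulated trials and the adjusted Cox model in 4.6 to 5.4%. Both hold the 5% level.

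**5. Chance imbalance.** The standard error of the difference in mean score is √(2/200) = 0.1 SD, so a 2-standard-error imbalance is 0.2 SD. Multiplied by an assumed 0.5 or 0.8, this is 0.10 or 0.16 in log hazard: exp(0.10) = 1.11 and exp(0.16) = 1.17, a shift of about 11 or 17%. An imbalance at least this large in either direction has a probability of roughly 5%.

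**6. What an interval adds.** Take a hypothetical 70/200 against 51/200. The difference is 0.095, z = 0.095 / 0.0459 = 2.07 and P = 0.039. The standard error is √(0.35 × 0.65/200 + 0.255 × 0.745/200) = 0.0457, so the 95% interval is 0.095 ± 1.96 × 0.0457, or 0.5 to 18.5 points. A P value below 0.05 is thus compatible with a trivial or a large absolute benefit.

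**7. Room for the covariates.** Treatment plus six covariates is seven parameters; 105 / 7 = 15 expected events per parameter at the planned effect.

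**The case against.** The strongest reply is that nothing stated is wrong. An intention-to-treat log-rank test with Kaplan-Meier curves is a standard primary comparison and holds its error rate. Adjustment is an efficiency choice, and at the trial's own design effect it buys about 1 point. All of this stands.

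Four stronger readings are tempting and not supported:
- **That the trial loses material power.** This is not so at the planned 50% reduction. It needs a smaller true effect together with fairly strong predictors.
- **That strong predictors are ignored.** The article gives no prognostic strength for any of these variables. Listing a factor for subgroups does not show that it predicts outcome, and the Background describes the prognostic picture for viability and left ventricular dysfunction as mixed.
- **That imbalance biases the result.** Randomization and the log-rank null distribution already allow for it.
- **That no estimate will be available.** Kaplan-Meier curves and event proportions are arm-level estimates, and the planned subgroup analyses presuppose some measure of treatment effect. Only a named contrast with its interval is absent, and a condensed article may leave that to the full protocol or analysis plan.

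It is also fair to say that changing the primary analysis after an interim look is more than an editorial matter. That stands and shapes the fix.

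The reply does not remove the point that the article states an unadjusted comparison when the data for a more efficient one are already collected. A smaller effect is also not far-fetched: the Background reports that most earlier trials of routine angioplasty after thrombolysis did not improve clinical outcome.

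**Conclusion.** The point holds as a low-cost improvement and not as an error. The stated comparison is valid and unadjusted. With 200 per arm, adjustment adds about 1 point or less at a 50% reduction, where power is already about 98%, and roughly 0 to 10 points at a reduction of about one third, where unadjusted power is about 73%. These figures assume a 35% three-year risk in the conservative arm, proportional hazards given the covariates, and a predictor strength that the article does not supply; with weak predictors the gain is close to nil. The absence of a named hazard ratio and interval is mainly reporting detail and would not be a finding by itself.

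**What to change.** Prespecify, for the composite endpoint in the intention-to-treat population, a Cox model with treatment, age, sex, diabetes, anterior infarction, thrombolytic use and baseline ejection fraction, with age and ejection fraction continuous. Leave out time from symptom onset to treatment: it is undefined for patients without reperfusion and would follow randomization if it refers to the PCI.

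Report the adjusted hazard ratio with 95% confidence interval and the Kaplan-Meier absolute risk difference with its interval. Name three years as the horizon, in line with the abstract, since the Statistical analysis section lists only 30 days, 6 months and 1 year. Base any statement about clinical importance on these intervals. Keep the unadjusted log-rank test beside the model as a sensitivity analysis.

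Date the change, record that it follows the interim analysis, state which test the interim rule used, and finalise it before anyone sees unblinded final data.

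The cost is a few sentences and no new data. The downsides are a documented change of analysis during the trial and a hazard ratio that is conditional on the covariates. The latter is why the unadjusted test and the absolute risk difference are reported alongside.

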**Methods:**

The VIAMI-study is designed as a prospective, multicenter, randomized, controlled clinical trial. Patients who are hospitalized with an acute myocardial infarction and who did not have primary or rescue PCI, undergo viability testing by low-dose dobutamine echocardiography (LDDE) within 3 days of admission. Consequently, patients with demonstrated viability are randomized to an invasive or conservative strategy. In the invasive strategy patients undergo coronary angiography with the intention to perform PCI with stenting of the infarct-related coronary artery and concomitant use of abciximab. In the conservative group an ischemia-guided approach is adopted (standard optimal care).

The primary end point is the composite of death from any cause, reinfarction and unstable angina during a follow-up period of three years.

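### The primary endpoint is defined over three years, but the primary analyses are listed only at 30 days, 6 months and 1 year, with none named as confirmatory

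*Protocol article*

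**What the plan says.** Five places in the protocol article bear on the horizon.

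- Abstract, Methods: "The primary end point is the composite of death from any cause, reinfarction and unstable angina during a follow-up period of three years".
- Study design: "The primary endpoint is the composite of death from any cause, recurrent infarction, and unstable angina". No horizon is attached here.
- Follow-up: "Patients will be followed for a period of three years".
- Statistical analysis: "A primary endpoint analysis is planned at 30 days, 6 months, and 1 year of follow-up". The same section plans Kaplan-Meier curves with a log-rank test, without saying up to what time, and makes intention-to-treat the basis of all analyses.
- Statistical design: "The expected event rate in the viability positive group is estimated to be 35 percent". The target is that "PCI leads to a 50% reduction in event rate in the invasive group compared to the conservative group", with 80% power at a two-sided alpha of 0.05, for which "200 patients will be needed in each group". No time is given for the 35%. An interim analysis after 200 patients may stop the trial at P ≤ 0.01.

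Current status adds that the interim analysis has been done, on 200 patients with 30 days of follow-up, and that the trial continued.

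**The concern.** The abstract and the analysis section fix different things. All three listed primary analyses fall before the horizon that defines the endpoint, and the analysis at that horizon is not listed. None of the three is called decisive, and none is called descriptive. An analysis plan that follows one section departs from the other, so a fuller document cannot resolve this without overriding part of the article.

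The stake is which result counts. Suppose the 6-month comparison were significant and the 1-year or three-year comparison were not. The text as it stands would allow the first to be reported as the primary result.

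The horizon could also affect the answer. Table I counts reinfarction around a revascularization procedure as a primary event, and the invasive arm is taken to angiography promptly after randomization, whereas the hypothesized benefit is the prevention of later events. The article gives no event timing, so a reversal over time is plausible but not shown.

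**Working it through.** **1. Horizon, place by place**

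| Item | Horizon stated |
|---|---|
| Primary endpoint, abstract | 3 years |
| Primary endpoint, Study design | none |
| Follow-up | 3 years |
| Primary endpoint analyses | 30 days, 6 months, 1 year |
| Log-rank test | none |
| 35% planning rate | none |
| Interim analysis as performed | 30 days |

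**2. Does the sample size reveal the horizon?** Take p1 = 0.35, p2 = 0.35 × 0.5 = 0.175, mean p = 0.2625, two-sided alpha 0.05 and power 80%.

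n per group = [1.96·√(2·0.2625·0.7375) + 0.842·√(0.35·0.65 + 0.175·0.825)]² / 0.175²

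= [1.96·0.622 + 0.842·0.610]² / 0.0306 = 3.00 / 0.0306 ≈ 98, or 99 after rounding up from unrounded values.

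A continuity correction gives 110. The stated 200 per group is not reproduced from the stated inputs. That is a separate matter, but it means the sample size cannot be used to work out which time point the trial was powered for.

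**3. Type I error if every listed time point could win.** Two assumptions are needed that the article does not state: each time point is tested at two-sided 0.05, and any one significant result counts as success. On accumulating events the test statistics are approximately multivariate normal, with correlation √(t_i / t_j) for t_i < t_j, where t is the share of events accrued. The overall error is the probability that at least one |Z| exceeds 1.96. The t values are assumptions, varied over a wide range, and each probability was simulated with 4 million draws.

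With t = 0.3, 0.7, 1, for example, the correlations are √(0.3/0.7) = 0.65, √0.3 = 0.55 and √0.7 = 0.84.

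| Tests counted | Assumed share of events | Overall type I error |
|---|---|---|
| 30 d, 6 m, 1 y | 0.7, 0.9, 1 (of 1-year events) | 8.4% |
| same | 0.5, 0.8, 1 | 9.7% |
| same | 1/3, 2/3, 1 | 10.7% |
| same | 0.3, 0.7, 1 | 10.8% |
| same | 0.1, 0.5, 1 | 12.3% |
| the three plus 3 y | 0.5, 0.7, 0.8, 1 (of 3-year events) | 10.5% |
| same | 0.2, 0.45, 0.65, 1 | 13.1% |
| same | 0.05, 0.3, 0.5, 1 | 14.9% |

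As a ceiling, three independent tests would give 1 − 0.95³ = 14.3%.

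**4. Comparison if one time point is decisive.** One prespecified test at 0.05 has an error of 5%. A single three-year test at 0.05 plus the interim at 0.01, with the final level unadjusted, gives 5.5% if the interim holds 50% of the final events and 5.9% if it holds 5%.

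**5. If all three listed times were meant to count.** A common nominal level of about 0.022 at each would hold the total at 5% (0.3, 0.7, 1 assumed).

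**The case against.** The best defence is that the log-rank test has no cut-off, patients are followed for three years, and the abstract fixes that horizon. On this reading the log-rank test over full follow-up is the confirmatory analysis, and the three earlier dates are staged reports. A reader might infer from the Statistical analysis section that no three-year analysis is planned at all. The article does not support that: none is listed, which is weaker. But the staged-report reading is not stated either. The section calls the earlier dates primary endpoint analyses and identifies no final one.

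A reader might also infer that the trial has no error control. That is too strong as well. There is one stated alpha and an interim threshold of P ≤ 0.01. What is absent is any rule across the three follow-up times. Splitting or ordering alpha is often left to an analysis plan, which is not shown here, so that absence alone would be weak ground. The conflict of horizons does not depend on it.

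Finally, a reader might take a doubling of the false-positive risk as established. It is not. The article says only that analyses are planned at those times. It does not say that each is tested at 0.05 or that any one suffices. If the three-year test alone decides, the error is 5.5–5.9%.

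**Conclusion.** The contradiction holds on the text and needs no calculation: a three-year primary endpoint, primary analyses listed only up to 1 year, none named as confirmatory, and neither the log-rank test nor the 35% tied to a horizon. It should be fixed before any result is called primary.

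The error inflation is a conditional consequence. If each of the three times were tested at 0.05 and any one counted, overall type I error would be about 8–12%, about 11% in central cases. With a three-year test added it would be about 10–15%. Both ranges rest on assumed event timing. Confidence is high for the contradiction and does not extend to the inflation.

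**What to change.** Name one confirmatory analysis. The default that matches the abstract is the intention-to-treat log-rank test of time from randomization to first primary event, through three years. If the sponsor prefers 1 year, the endpoint definition in the abstract should be amended to match.

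Report the remaining time points as secondary, with estimates and confidence intervals and no claim of success. State the horizon to which the 35% refers, and make it the chosen one.

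Make the change by dated amendment, recording that it was made without knowledge of results by arm, because a 30-day interim look has already taken place.

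The change needs no extra patients. The cost is the amendment itself and the sponsor's option of claiming success at an early time point. In choosing the horizon, the sponsor should weigh that years two and three are followed by telephone, while the definitions of reinfarction and unstable angina rest on enzyme, ECG or hospital evidence.
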